**REVISION HISTORY**

| Version | Date | Amendment Text | Description |
| --- | --- | --- | --- |

Revision history is listed in Appendix A on page 2.

# 1. TRIAL SUMMARY

World Health Organization Registration Data Set

| Title | Innovative Support for Patients with SARS-COV-2 Infections Registry (INSPIRE): a longitudinal study of the medium and long-term sequelae of SARS-CoV-2 infection |
| --- | --- |
| Primary registry and trial identifying number | ClinicalTrials.gov Identifier: NCT04610515 |
| Secondary identifying numbers | 75D30120C08008 |
| Sources of monetary or material support | Centers for Disease Control and Prevention Financial and other support |
| Primary sponsor | Center for Disease Control and Prevention |
| Secondary sponsors (if any) | Not applicable |
| Central contact | [name]  Rush University  [contact] |

| Brief title | INSPIRE Registry |
| Acronym | Innovative Support for Patients with SARS-COV-2 Infections (COVID-19) Registry (INSPIRE) |
| Countries of recruitment | USA |
| Condition(s) or focus of study | SARS-COV-2-2 infection |
| Interventions | Not applicable |
| Key eligibility criteria | Age eligibility: 18 years or older |
| Study design | Allocation: N/A  Primary purpose: Other  Phase: Phase 3 |
| Masking | Not applicable |
| Date of enrollment | November 1, 2020 |
| Target sample size | 3600 |
| Recruitment status | Recruiting |
| Primary outcomes | To understand the medium- and long-term sequelae of symptomatic SARS-CoV-2 infection |
| Secondary outcomes | To describe predictors of sequelae as reported by individuals and as recorded in their EMR, and to assess the intersection of long-term sequelae of COVID-19 with other previously defined syndromes with overlapping features such as myalgic encephalomyelitis/chronic fatigue syndrome (ME/CFS) |

# 2. INTRODUCTION

## 2.1. Background and rationale

The COVID-19 pandemic is associated with considerable morbidity and mortality. As of May 2021, > 32.6 million COVID-19 cases and > 580,000 attributed deaths have been detected in the USA [[1]](https://www.spiritprotocol.com/api/docx/https://paperpile.com/c/nKRweq/D7DYc). Globally, > 160 million COVID-19 cases and > 3.3 million attributed deaths have been reported [[2]](https://www.spiritprotocol.com/api/docx/https://paperpile.com/c/nKRweq/0puKg). The clinical course of acute COVID-19 is well-described [[3–7]](https://www.spiritprotocol.com/api/docx/https://paperpile.com/c/nKRweq/lU1D+t8iR+K9mW+Mq1f+OJ8y). Post-acute COVID-19 is defined as persistence of symptoms or development of sequelae after 3 or 4 weeks from the onset of acute symptoms of COVID-19 [[8–10]](https://www.spiritprotocol.com/api/docx/https://paperpile.com/c/nKRweq/XHsQi+bmgL6+etRcB). This definition is further divided into subacute or ongoing symptomatic COVID-19, including symptoms from 4-12 weeks beyond acute COVID-19, and a chronic or post-COVID-19 syndrome, which includes symptoms persisting or present beyond 12 weeks of acute COVID-19 not attributable to alternative diagnoses [[8,11]](https://www.spiritprotocol.com/api/docx/https://paperpile.com/c/nKRweq/XHsQi+1Igm8). Information on post-acute COVID-19 and long-term sequelae of SARS-CoV-2 infection is only recently emerging [[12–15]](https://www.spiritprotocol.com/api/docx/https://paperpile.com/c/nKRweq/DBuqU+NqrkR+3wwBG+PRH0f).

To characterize post-COVID-19 syndromes better, there is an urgent need for broader representation in study population selection to allow for representativeness and generalizability, to set objective outcomes that are not limited to symptoms but include illness events and clinical events, and to include SARS-CoV-2 negative individuals to ensure other effects of the pandemic are considered in the analysis (e.g. impact on livelihoods, mental health, food security, and mobility) [[16]](https://www.spiritprotocol.com/api/docx/https://paperpile.com/c/nKRweq/38UeS). Such work will help clinicians know what post-infectious sequelae to expect and who is at increased risk, will help ensure research findings can be compared across studies, and will move us towards addressing critical health care response needs.

To accelerate research during this critical time in the global COVID-19 pandemic, our research consortium designed a prospective longitudinal study to use patient-reported information linked to real-world data through the Innovative Support for Patients With SARS-COV-2 Infections Registry (INSPIRE) hosted on a secure online platform (Hugo, Hugo Health LLC, Guilford, CT) which imports health information from various sources with permission from participants. In this study, researchers follow a sample of individuals under investigation for SARS-CoV-2 over time, to collect patient-reported outcomes, interactions with the medical system (i.e., clinic visits, hospitalizations, laboratory test and medications prescribed) and outcomes of care as reported in the electronic medical record (EMR).

## 2.2. Objectives

Our objectives are to understand the medium- and long-term sequelae of symptomatic SARS-CoV-2 infection, to describe predictors of sequelae as reported by individuals and as recorded in their EMR, and to assess the intersection of long-term sequelae of COVID-19 with other previously defined syndromes with overlapping features such as myalgic encephalomyelitis/chronic fatigue syndrome (ME/CFS).

## 2.3. Trial design

This is a prospective, multicenter, longitudinal cohort study of individuals with acute symptoms consistent with SARS-CoV-2, including those with positive and negative diagnostic SARS-CoV-2 tests to compare those with and without SARS-CoV-2 infection (ClinicalTrials.gov Identifier: NCT04610515) [[17]](https://www.spiritprotocol.com/api/docx/https://paperpile.com/c/nKRweq/WTVFx).

# 3. METHODS

## 3.1. Study setting

Participants are enrolled from any of eight regions across the United States led by investigators at Rush University (Chicago, Illinois), Yale University (New Haven, Connecticut), the University of Washington (Seattle, Washington), Thomas Jefferson University (Philadelphia, Pennsylvania), the University of Texas Southwestern (Dallas, Texas), the University of Texas, Houston (Houston, Texas), the University of California, San Francisco (San Francisco, California) and the University of California, Los Angeles (Los Angeles County, California). The recruitment areas vary in terms of the population served to allow for ethnic and geographic diversity among study participants. As enrollment is through the internet and can be completed without assistance of research staff support, participants include those who have never been to the clinic or hospital for their symptoms and others who have been to the emergency department or hospitalized. Additionally, participants with any digital health portal can enroll in this study; participants’ health portals need not be those directly linked to the academic institutions listed above.

## 3.2. Eligibility criteria

This study includes adult patients who are under clinical investigation for possible SARS-CoV-2 infection and who meet inclusion criteria outlined in Table 1. We include individuals with symptomatic presentation to determine comparative frequency of outcomes amongst symptomatic individuals with and without SARS-CoV-2 infection: symptomatic individuals presenting with covid-like illness who test negative will act as controls for symptomatic individuals who have positive tests for SARS-CoV-2. Asymptomatic individuals are not eligible, given the anticipated lower rates of outcomes among asymptomatic individuals who test positive for SARS-CoV-2, and the significant heterogeneity in reasons for testing in asymptomatic individuals, such as screening for social, educational, occupational reasons and prior to routine clinical procedures. Individuals who self-report symptoms suggestive of acute SARS-CoV-2 infection, and are tested for SARS-CoV-2 within the last 42 days, are eligible to participate. From study initiation through the summer of 2021, symptoms of acute SARS-CoV-2 was defined using the COVID-19 clinical criteria case definition (Table 2) [[18]](https://paperpile.com/c/nKRweq/MqHQg); beginning summer of 2021, in order to capture less symptomatic individuals, the inclusion criteria were revised to require only one symptom among those listed in Table 2. Individuals for whom a SARS-CoV-2 test result cannot be confirmed are not eligible to participate in the study. Efforts are made to recruit participants from across the spectrum of COVID-19 illness severity, including individuals from outpatient (e.g., drive through testing with self-reported symptoms) to inpatient settings, and those cared for in intensive care units. We seek to enroll using a 3:1 case/control ratio to oversample those who are positive for SARS-CoV-2 on testing, while still ensuring an adequate control cohort for comparison.

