**Table 1: Inclusion and exclusion criteria**

Inclusion criteria:

1. Fluent in English or Spanish
2. Age 18 years or older
3. Self-reported symptom suggestive of acute SARS-CoV-2 infection [[19]](https://www.spiritprotocol.com/api/docx/https://paperpile.com/c/nKRweq/KvIKQ)
4. Tested for SARS-CoV-2 with any FDA-approved or authorized viral test (i.e., nucleic acid amplification test or antigen test [[20]](https://www.spiritprotocol.com/api/docx/https://paperpile.com/c/nKRweq/mGkhJ)) within 42 days of enrollment

Exclusion criteria:

1. Unable to provide informed consent
2. Study team unable to confirm the result of a diagnostic test for SARS-CoV-2
3. Does not have access to a hand-held device or computer that would allow for digital participation in the study
4. Lawfully imprisoned while participating in the study

**Table 2: COVID-19 clinical criteria case definition (August 2020)** [[18]](https://www.spiritprotocol.com/api/docx/https://paperpile.com/c/nKRweq/MqHQg)

*In the absence of a more likely diagnosis,*

At least TWO of the following symptoms:

- Fever (measured or subjective)
- Chills
- Rigors
- Myalgia
- Headache
- Sore throat
- Nausea or vomiting
- Diarrhea
- Fatigue
- Congestion or runny nose

Or any ONE of the following symptoms:

- Cough
- Shortness of breath
- Difficulty breathing
- New olfactory disorder
- New taste disorder

Or severe respiratory illness with at least ONE of the following:

- Clinical or radiographic evidence of pneumonia
- Acute respiratory distress syndrome (ARDS)

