We will use statistical analyses to address the risk of ME/CFS and other health conditions in those with versus without SARS-CoV-2 infection as risk difference or risk ratios or odds ratios, as appropriate. We will also adjust for additional patient-level factors of interest, including age, sex, race/ethnicity, income, and presence of specific underlying conditions such as hypertension and diabetes. We anticipate that as more is learned about the clinical courses of persons with symptomatic SARS-CoV-2 infection, additional covariates of interest available from electronic record data will be assessed for their association with adverse outcomes.

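### The uninfected comparator is defined by one negative viral test, so people known to have been infected earlier can be counted as controls, which would attenuate the contrast

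*Protocol*

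**What the plan says.** Protocol section 2.3 gives the purpose of the two groups as "to compare those with and without SARS-CoV-2 infection". Section 3.2 defines the comparator: "symptomatic individuals presenting with covid-like illness who test negative will act as controls for symptomatic individuals who have positive tests for SARS-CoV-2".

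Entry rests on two facts. Table 1 asks for a "Self-reported symptom suggestive of acute SARS-CoV-2 infection" and a viral test ("i.e., nucleic acid amplification test or antigen test"). On timing, section 3.2 says that people who "are tested for SARS-CoV-2 within the last 42 days, are eligible to participate". Table 1 has four exclusions, and the only one about testing is "Study team unable to confirm the result of a diagnostic test for SARS-CoV-2". None concerns an earlier positive test or an earlier COVID-19 diagnosis.

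Under Table 2, cough or shortness of breath alone qualified from the start. From summer 2021, "the inclusion criteria were revised to require only one symptom among those listed in Table 2", so fatigue or headache alone also qualifies.

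Section 3.9.1 groups participants by their initial test result and will express the risk of ME/CFS and other conditions "in those with versus without SARS-CoV-2 infection as risk difference or risk ratios or odds ratios". The adjustment factors named there are age, sex, race/ethnicity, income and underlying conditions such as hypertension and diabetes. Prior SARS-CoV-2 infection is not named. The enrolment row of the timeline in section 3.14 does not list it either.

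**The concern.** A negative viral test shows that the virus was not detected on that day. It does not show that the person was never infected. Enrolment began in November 2020 and was still open after summer 2021, so some people tested for a new complaint will have had COVID-19 before.

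Several Table 2 symptoms are also outcomes of the study. Section 3.5 names dyspnea and cough as post-infectious sequelae, and fatigue is central to the ME/CFS criteria in Table 3. A person with persisting sequelae of an earlier infection can therefore report one of them as the entry symptom, test negative and join the comparator. Table 3 requires impairment for more than six months, which such a person could reach soon after entry.

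If these controls have more events than never-infected controls, the comparator's event rate rises and the contrast moves towards no difference. Enrolling more people does not remove that bias. This is misclassification at entry, distinct from controls who become infected during follow-up.

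**Working it through.** **Inputs from the protocol (section 3.8).** Positive group n1 = 3,600; negative group n0 = 1,200; negative-group rate 2.5%; absolute difference 2.5 points, hence 5.0% in the positive group; alpha 0.05; stated power 97.8%.

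**Inputs that are assumptions.** f, the share of controls with an earlier infection, and r, their outcome rate. The protocol gives neither.

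**Step 1. Reproduce the stated power.** Use a two-sided pooled test of two proportions without continuity correction:

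power = Φ[(d − 1.96 × SE0) / SE1]

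- Pooled rate = (1,200 × 0.025 + 3,600 × 0.05) / 4,800 = 0.04375
- SE0 = √[0.04375 × 0.95625 × (1/1,200 + 1/3,600)] = 0.006818
- SE1 = √[0.025 × 0.975/1,200 + 0.05 × 0.95/3,600] = 0.005789
- Power = Φ[(0.025 − 1.96 × 0.006818) / 0.005789] = Φ(2.01) = 97.8%

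This matches the protocol. The figure assumes f = 0.

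**Step 2. Earlier infections among controls only.** Control rate = (1 − f) × 2.5% + f × r, with the positive group held at 5.0%.

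| f | r | Control rate | Difference (points) | Risk ratio | Power |
|---|---|---|---|---|---|
| 5% | 5% | 2.625% | 2.375 | 1.90 | 96% |
| 10% | 5% | 2.75% | 2.25 | 1.82 | 94% |
| 20% | 5% | 3.0% | 2.0 | 1.67 | 85% |
| 10% | 10% | 3.25% | 1.75 | 1.54 | 73% |
| 20% | 10% | 4.0% | 1.0 | 1.25 | 28% |
| 10% | 20% | 4.25% | 0.75 | 1.18 | 17% |

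When r equals the positive-group rate of 5%, the difference shrinks by the factor (1 − f), and power falls below 80% at about f = 25%.

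**Step 3. The same share and rate in both groups.** Table 1 admits previously infected people as cases too. Positive-group rate = (1 − f) × 5.0% + f × r.

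| f | r | Positive vs control | Difference (points) | Power |
|---|---|---|---|---|
| 10% | 10% | 5.5% vs 3.25% | 2.25 | 90% |
| 20% | 10% | 6.0% vs 4.0% | 2.0 | 77% |
| 10% | 20% | 6.5% vs 4.25% | 2.25 | 84% |

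The difference is still (1 − f) × 2.5 points, so equal mixing reduces the attenuation in the enriched scenarios but does not cancel it.

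**Step 4. Cost of removing such controls.** If 20% are removed, 1,200 × 0.8 = 960 remain. With 3,600 positives and 5.0% versus 2.5%, the same formula gives 95% power.

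**The case against.** Several parts of the text work against this route. Section 2.3 describes a cohort with acute symptoms, and Table 1 asks for symptoms suggestive of acute infection. Table 2 applies only when no other diagnosis is more likely, and it requires smell or taste disorder to be new. Sites that screen the medical record look at the reason for testing, and section 3.3 aims to enrol close to the initial test. Fatigue dating from a known infection the previous winter is not plainly an acute symptom. These words narrow the route. They do not close it, because symptoms are self-reported, section 3.1 allows enrolment without staff, and no rule refers to infection history.

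A second objection is that the SAP, which is not shown, may define the analysis groups, and that linked portals already supply test results and diagnoses. Section 3.8 also frames the ME/CFS comparison as incidence, so leaving out prevalent cases would be a natural analysis step. This is fair for the analysis rule. It does not cover eligibility or what is asked at enrolment: participants choose which portals to link, and tests by city or state agencies may not appear in them.

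A reader might infer that the contrast is likely to be severely weakened or even reversed. The documents do not support that. The lowest powers in Step 2 (73%, 28%, 17%) require earlier infections to affect controls only; with equal mixing they become 90%, 77% and 84%. No scenario tabulated here reverses the difference. With f = 10% among controls only, reversal would need r above 2.5% + 2.5%/0.10 = 27.5%. Nor did the summer 2021 change create the route, since cough or shortness of breath alone already qualified.

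**Conclusion.** The gap is real: as written, the protocol lets a person with a known earlier positive test be analysed as uninfected. The direction is towards no difference, provided that previously infected controls have more events than never-infected ones.

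The size cannot be fixed from the documents. At 5% of controls with a 5% rate the loss is minor: 0.125 points, with power at 96%. At 10% of controls it ranges from 2.25 points and 94% power (5% rate) to 1.75 points and 73% (10% rate, controls only); if cases are affected equally at the 10% rate, it is 2.25 points and 90%.

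This should be fixed, because it concerns who makes up the comparison group and the remedy is cheap. With the share and outcome rate unknown and partial safeguards in place, it does not amount to a fatal flaw.

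**What to change.** 1. At enrolment, ask about any earlier positive SARS-CoV-2 test or COVID-19 diagnosis, and query the linked medical records for the same.
2. State in sections 3.2 and 3.9.1 that controls with a known earlier positive are left out of the uninfected comparator and reported as a separate group. Apply this to those already enrolled.
3. Flag cases with an earlier positive, but keep them in the main contrast. Removing them would change the case population from symptomatic infection to first known infection, which the objectives in section 2.2 do not require.
4. Add a sensitivity analysis restricted to participants in both groups without known prior infection.

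The cost is one enrolment question, a query of data already being collected, and short additions to two sections. Some controls are lost to the comparator; about 95% power remains if 20% are removed and the other assumptions hold. Earlier infections that were never recorded will remain, and the report should say so.

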**Table 1: Inclusion and exclusion criteria**

Inclusion criteria:

1. Fluent in English or Spanish
2. Age 18 years or older
3. Self-reported symptom suggestive of acute SARS-CoV-2 infection [[19]](https://www.spiritprotocol.com/api/docx/https://paperpile.com/c/nKRweq/KvIKQ)
4. Tested for SARS-CoV-2 with any FDA-approved or authorized viral test (i.e., nucleic acid amplification test or antigen test [[20]](https://www.spiritprotocol.com/api/docx/https://paperpile.com/c/nKRweq/mGkhJ)) within 42 days of enrollment

Exclusion criteria:

1. Unable to provide informed consent
2. Study team unable to confirm the result of a diagnostic test for SARS-CoV-2
3. Does not have access to a hand-held device or computer that would allow for digital participation in the study
4. Lawfully imprisoned while participating in the study

**Table 2: COVID-19 clinical criteria case definition (August 2020)** [[18]](https://www.spiritprotocol.com/api/docx/https://paperpile.com/c/nKRweq/MqHQg)

*In the absence of a more likely diagnosis,*

At least TWO of the following symptoms:

- Fever (measured or subjective)
- Chills
- Rigors
- Myalgia
- Headache
- Sore throat
- Nausea or vomiting
- Diarrhea
- Fatigue
- Congestion or runny nose

Or any ONE of the following symptoms:

- Cough
- Shortness of breath
- Difficulty breathing
- New olfactory disorder
- New taste disorder

Or severe respiratory illness with at least ONE of the following:

- Clinical or radiographic evidence of pneumonia
- Acute respiratory distress syndrome (ARDS)

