## 3.6. Data collection

### 3.6.1. Trial procedures and evaluations

Results for a SARS-CoV-2 viral test (i.e., nucleic acid amplification test or antigen test) are confirmed by the research staff either through visualizing the result in the EMR or by reviewing an image of the test result sent to the research staff by the participant. After an eligible patient enrolls in the study, a combination of self-reported information and information generated from the patient’s own health information is connected to the Hugo platform, collected, and sent to the study site over the 18-month follow-up period (Appendix A).

Self-reported data: Using Hugo, surveys including the variables outlined above are sent by electronic mail or text to participants at the research site every 3 months throughout the follow-up period. These responses are sent through the Hugo platform and then shared with the study team. Subjects use their personal smartphone, tablet, computer, or other electronic device to connect to the internet and answer surveys that ascertain their symptoms, health care use, health care experience, and physical, mental, and social health over an 18-month period. Responses sent by participants are encrypted. To minimize participant burden, each data collection episode is designed to take approximately 15 minutes or less to complete.

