## 3.8. Sample size

Our target enrollment is 3,600 people with SARS-CoV-2 infection confirmed by a positive SARS-CoV-2 viral test (i.e., nucleic acid amplification test or antigen test) and 1,200 people with a negative SARS-CoV-2 viral test. We expect that the age distribution of enrolled subjects will represent that of patients tested in each site. Four of the sites (Yale, Jefferson, Rush and UW) draw on smaller catchment populations so have planned enrollment of 400 subjects per site (300 individuals with SARS-CoV-2 and 100 individuals without SARS-CoV-2). Four sites (UT Southwestern, UT Houston, University of California, San Francisco, and University of California, Los Angeles) have larger catchment populations so have planned enrollment of 800 subjects per site (600 individuals with SARS-CoV-2 and 200 individuals without SARS-CoV-2).

We estimated the power to detect relative differences in outcome rates between those who are symptomatic and test positive for SARS-CoV-2 as compared to those who are symptomatic but test negative for SARS-CoV-2. These power calculations are agnostic to the outcome of interest but based on the aim to examine relative differences in long-term outcomes between individuals with and without SARS-CoV-2 based on and between age strata. For comparison of ME/CFS incidence in SARS-CoV-2 infected vs uninfected, power calculations are based on the null hypothesis that there is no difference between individuals with and without SARS-CoV-2 in the outcome rate.

The assumptions used to generate these power calculations include both elements outside the study’s team’s control (e.g., baseline outcome rate in individuals without SARS-CoV-2) as well as elements amenable to changes in study design (e.g., individuals with SARS-CoV-2 strata group size).  Assumptions include:

- 3,600 individuals with SARS-CoV-2 and 1,200 individuals without SARS-CoV-2
- Baseline outcome rate in individuals without SARS-CoV-2: 2.5% with the contingency that the baseline outcome rate may vary between age strata (18-40 years, 41-64 years, ≥ 65 years)
- Outcome rate in individuals with SARS-CoV-2: presented as scenarios based on absolute or relative differences from baseline outcome rate in individuals without SARS-CoV-2. Also presented under the likely scenario that outcome rates vary between age strata
- Alpha = 0.05 (fixed)

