## 3.9. Statistical methods

### 3.9.1. Outcomes

Statistical analyses will describe disease course and outcomes, including the characterization of specific symptoms and duration of symptoms, health care utilization (emergency department, hospitalization, post-acute care) with clinical (morbidity/mortality) and patient-reported health status outcomes as well as recovery (early and late disease sequelae). Baseline and demographic characteristics will be summarized by descriptive summaries (e.g., means and standard deviations for continuous variables such as age and percentages for categorical variables such as gender, medians, and quartiles for skewed data). Analyses will:

- Compare health status at baseline and follow-up between persons in the same age group who test SARS-CoV-2 positive and negative at initial test.
- Characterize health care utilization (ambulatory and ED visits, hospitalizations, post-acute care, telehealth visits) among SARS-CoV-2 positive participants by age and compare these to SARS-CoV-2 negative participants.
- Characterize and compare health outcomes by age and SARS-CoV-2 status: emergency or ambulatory care, admission to hospital); ICU-free survival;^16^ hospital-free survival; and subsequent patient-reported health status (cognition; physical health; mental health; and return to work).

We will use statistical modeling to estimate the association between key covariates and outcomes, including evaluating interactions by age. We plan to use survival analysis techniques to analyze time to outcome events, logistic regression for binary outcomes (e.g., hospitalization versus no hospitalization), Poisson or Cox regression for count data (e.g., number of hospitalizations over time), and linear regression models for continuous outcomes (e.g., PROMIS-29). Multiple imputation will be considered to handle missing covariate and outcome data in these analyses [[43]](https://www.spiritprotocol.com/api/docx/https://paperpile.com/c/nKRweq/3dpny). Chained equations will be used to impute each variable with missing data. Sensitivity analyses will be conducted using missing categories for covariates and including only people with non-missing outcome information.

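### Grouping by the initial test result, with either test type accepted, can place infected people among the controls and bias the main contrast toward no difference

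*Protocol*

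**What the plan says.** Three parts of the protocol together define the comparison groups.

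- **Entry.** Table 1 requires that a participant be "Tested for SARS-CoV-2 with any FDA-approved or authorized viral test (i.e., nucleic acid amplification test or antigen test"), within 42 days of enrolment. A negative result of either type has the same standing.
- **Control definition.** Section 3.2: "symptomatic individuals presenting with covid-like illness who test negative will act as controls for symptomatic individuals who have positive tests for SARS-CoV-2". Section 3.8 plans for "1,200 people with a negative SARS-CoV-2 viral test". No second or confirmatory test is mentioned.
- **Grouping in the analysis.** The first analysis bullet of section 3.9.1 compares people "who test SARS-CoV-2 positive and negative at initial test". The other bullets refer to SARS-CoV-2 status without defining it differently.

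The label then changes. The power assumptions in section 3.8 call the second group individuals without SARS-CoV-2, and section 3.9.1 estimates the risk of ME/CFS and other conditions "in those with versus without SARS-CoV-2 infection as risk difference or risk ratios or odds ratios".

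Section 3.6.1 says results "are confirmed by the research staff either through visualizing the result in the EMR or by reviewing an image of the test result". This establishes that the reported result is genuine, not that a test-negative person was uninfected. The adjustment factors named in section 3.9.1 are patient-level, "including age, sex, race/ethnicity, income, and presence of specific underlying conditions such as hypertension and diabetes". The sensitivity analyses named there concern missing data.

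**The concern.** The protocol equates a negative initial test with absence of infection and has no rule for discordant results within one illness. Enrolment may follow the test by up to 42 days, so a negative test followed by a positive one before enrolment is possible. As written, that participant is a control.

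The controls are chosen because they have a covid-like illness, so the chance that a negative is false cannot be dismissed. A missed infection in the control group brings some or all of the case group's outcome risk with it. That shrinks every risk difference, risk ratio and odds ratio for positive versus negative, including the ME/CFS comparison. A larger sample does not remove this bias.

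Infections before the index illness, or acquired during the 18-month follow-up, are separate matters and are not part of this point.

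**Working it through.** **Inputs from the protocol (section 3.8).** 3,600 positive and 1,200 negative; outcome rate 2.5% without infection; difference 2.5 points, so 5.0% with infection; alpha 0.05 (two-sided reproduces the stated figure); stated power 97.8%.

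**Inputs that are assumptions.** Infection prevalence among symptomatic people tested, 20–40%; antigen sensitivity, 50–80%; nucleic acid (NAAT) sensitivity, 95%; specificity 1; share of controls classified by antigen test, 25–100%. The protocol gives none of these.

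**Step 1: reproduce the stated power.** Pooled two-proportion test:
- pooled rate = (1,200 × 0.025 + 3,600 × 0.05)/4,800 = 0.04375
- null standard error = √[0.04375 × 0.95625 × (1/1,200 + 1/3,600)] = 0.006818
- alternative standard error = √[0.025 × 0.975/1,200 + 0.05 × 0.95/3,600] = 0.005789
- z = (0.025 − 1.960 × 0.006818)/0.005789 = 2.010, so power = 97.8%, as stated. This figure assumes no misclassified controls.

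**Step 2: share of negatives who are infected.** With prevalence p and sensitivity Se, share = p(1 − Se)/[p(1 − Se) + (1 − p)].
- p = 0.2, Se = 0.8: 0.04/0.84 = 4.8%
- p = 0.3, Se = 0.7: 0.09/0.79 = 11.4%
- p = 0.4, Se = 0.5: 0.20/0.80 = 25.0%
- NAAT, Se = 0.95: 1.2%, 2.1% and 3.2% at p = 0.2, 0.3 and 0.4

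If a fraction a of controls was antigen-tested, the overall share is m = a × (antigen share) + (1 − a) × (NAAT share).

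**Step 3: effect on the contrast.** If missed infections carry the full case-group risk, the observed control rate is 2.5% × (1 + m). The observed difference is then 2.5 × (1 − m) points and the observed risk ratio is 2/(1 + m). Each 1% of infected controls thus removes 1% of the true difference.

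| p, antigen Se | Antigen share of controls | m | Difference (points) | Risk ratio | Power |
|---|---|---|---|---|---|
| 20%, 80% | 25% | 2.1% | 2.45 | 1.96 | 97.2% |
| 20%, 80% | 50% | 3.0% | 2.43 | 1.94 | 96.9% |
| 20%, 80% | 100% | 4.8% | 2.38 | 1.91 | 96.2% |
| 30%, 70% | 25% | 4.4% | 2.39 | 1.92 | 96.3% |
| 30%, 70% | 50% | 6.8% | 2.33 | 1.87 | 95.3% |
| 30%, 70% | 100% | 11.4% | 2.22 | 1.80 | 92.7% |
| 40%, 50% | 25% | 8.7% | 2.28 | 1.84 | 94.3% |
| 40%, 50% | 50% | 14.1% | 2.15 | 1.75 | 90.7% |
| 40%, 50% | 100% | 25.0% | 1.88 | 1.60 | 79.7% |

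**Step 4: relax full carry-over.** If missed infections carry only half the excess risk, the last row's control rate is 2.5% × (1 + 0.125) = 2.81%, and power is 91.9% rather than 79.7%.

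**Step 5: a comparison with less reserve.** The protocol's own 80% design (10% versus 5%, 918 and 306 participants) reproduces at 80.1%. With m = 5% it falls to 74.9%, and with m = 10% to 69.2%.

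**The case against.** The strongest reply is that this is an openly stated test-negative comparison, that the named sensitivity analyses belong in an SAP that is not at hand, and that the premise about antigen tests comes from outside the document. Much of this stands, and it limits what can be claimed.

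- A reader might infer that test type is not recorded. The protocol does not say so. Staff view the result itself (section 3.6.1), and the platform imports test orders and results.
- A reader might infer that no planned analysis could reveal the problem. That cannot be claimed with the SAP unseen, and section 3.9.1 leaves room for further covariates from the electronic record.
- A reader might take 80% power as the expected loss. It needs 40% prevalence, 50% sensitivity, all controls antigen-tested and full risk carry-over together. NAAT false negatives also contribute: at 30% prevalence, all-NAAT controls would already include 2.1% infected.
- The lower sensitivity of antigen tests is an assumption here, and so is the presence of missed infections in any given number.

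The objection does not remove the core of the point. The control definition and the grouping by initial result are design choices fixed in the protocol. They would send a participant with a known positive test in the same illness to the uninfected group, whichever test type was used.

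**Conclusion.** The concern holds in a limited form. The protocol's grouping rule allows infected people to be analysed as controls, including some whose infection was documented before enrolment, and the resulting bias is toward no difference. The protocol does not determine its size. Under the stated assumptions, with 25–50% of controls antigen-tested, the risk ratio of 2.0 would be seen as about 1.75 to 1.96, and overall power would be about 91% to 97% against the stated 97.8%. The fall to 80% and a risk ratio of 1.6 is an extreme corner. The main harm is therefore a biased estimate; the overall power mostly survives. Comparisons with less reserve, such as smaller effects or those within age strata, would lose more. The correction is cheap and worth making.

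**What to change.** 1. In section 3.9.1, replace grouping by the initial test with this rule: a participant is SARS-CoV-2 positive if any viral test during the index illness up to enrolment was positive. Define the index illness; the existing 42-day entry window could bound it. Use the same definition in sections 3.2 and 3.8.
2. Keep index test type (NAAT or antigen), taken from the result staff already view, as an analysis variable.
3. Add a sensitivity analysis of the positive-versus-negative comparisons, restricted to participants classified by NAAT **in both groups** and adjusted for site and calendar period. Restricting controls alone would change the make-up of one group only.

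**Cost.** One classification rule, one variable and one extra run per comparison. The restricted run has fewer participants and wider intervals. It may also shift the mix of care settings, so a changed estimate would not isolate misclassification. Reclassification depends on how often people were tested and which portals they linked. That may vary with health care use, which is itself an outcome, and this should be stated when the results are reported.
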